## Abstract

**Background:**

Patients undergoing liver transplantation with preexisting renal dysfunction are prone to further renal impairment with the early postoperative use of Calcineurin-inhibitors. However, there is only little scientific evidence for the safety and efficacy of de novo CNI free "bottom-up" regimens in patients with impaired renal function undergoing liver transplantation. This is a single-center study pilot-study (**PATRON07**) investigating safety and efficacy of CNI-free, "bottom-up" immunosuppressive (IS) strategy in patients undergoing liver transplantation (LT) with renal impairment prior to LT.

**Methods/Design:**

Patients older than 18 years with renal impairment at the time of liver transplantation eGFR < 50 ml/min and/or serum creatinine levels > 1.5 mg/dL will be included. Patients in will receive a CNI-free combination therapy (basiliximab, MMF, steroids and delayed Sirolimus). Primary endpoint is the incidence of steroid resistant acute rejection within the first 30 days after LT. The study is designed as prospective two-step trial requiring a maximum of 29 patients. In the first step, 9 patients will be included. If 8 or more patients show no signs of biopsy proven steroid resistant rejection, additional 20 patients will be included. If in the second step a total of 27 or more patients reach the primary endpoint the regimen is regarded to be safe and efficient.

**Discussion:**

If a CNI-free-"bottom-up" IS strategy is safe and effective, this may be an innovative concept in contrast to classic top-down strategies that could improve the patient short and long-time renal function as well as overall complications and survival after LT. The results of **PATRON07 **may be the basis for a large multicenter RCT investigating the new "bottom-up" immunosuppressive strategy in patients with poor renal function prior to LT.

http://www.clinicaltrials.gov-identifier: NCT00604357

## Background

### Medical Problem

Early renal dysfunction after liver transplantation (LT) is reported with a frequency as high as 50% [1,2]. The introduction of the MELD-based allocation system in the Eurotransplant area in December 2006 led to an increase of the proportion of liver transplant recipients with renal dysfunction at the time of transplantation, since creatinine became a key component for the allocation of liver allografts [3]. Major risk factors associated with early posttransplant renal impairment are: preexisting diabetes mellitus, time on the waiting list with end-stage hepatic disease, application of blood products, liver allograft dysfunction and toxicity of Calcineurin-inhibitors (CNI) [4-11]. The risk of developing chronic renal failure after LT is approximately 20% after 5 years, associated with the use of CNI and a 4-fold increased mortality risk[12] - and these are data from the pre-MELD era. An additional problem in this specific patient group (impaired renal function at the time of LT and MELD-scores of 25 and/or higher), is a high risk for developing infectious complications [13]. Studies indicate that early infections are present in almost 85% of all patients, and become the most common cause of death early after transplantation. Notably, two-third of infections in liver transplant patients occur within the first 3 months after transplantation with a very high percentage (67%) of severe infections [14,15]. In general, the inflammatory response associated with infection is impaired by immunosuppressive drugs. This disturbed regulation increases the susceptibility for a broad range of normal and of opportunistic infections [13]. Therefore, patients with high lab-MELD scores hypothetically should require a rather low amount of immunosuppressive (IS) drugs during the first days to weeks after transplantation, while they are in a state of SIRS (systemic inflammatory response syndrome)-like state [16,17].

### Current treatment options

Most patients undergoing liver transplantation are treated with de-novo immunosuppressive protocol based on a CNI (cyclosporine or tacrolimus) and one or two additional drugs like steroids, mycofenolate mofetil (MMF) or induction therapy with anti-thymocyte globulin or anti-CD25-monoclonal antibodies. Current paradigms are based on a top-down strategy which is based on initially high dose IS treatment with a reduction in case of side-effects or complications. One of the major adverse effects of CNI is nephrotoxicity, a deleterious complication for long-term survival and quality of life [13-15]. However, there are no IS approaches that concentrate on a complete avoidance or "bottom-up" strategy, delaying the introduction of CNI or an mTOR-inhibitor until the patient really does require additional IS (acute rejection). To date there is only one prospectively randomized trial that investigated the influence of delayed, low-dose IS with Tacrolimus and MMF in patients with normal renal function. In this trial patients did profit from an early avoidance of Tacrolimus with regards to renal function [18].

### Aim of the pilot trial

The primary aim of this study concept is **(I) **to evaluate, if a de novo CNI-free IS regimen in patients with preexisting renal impairment at the time-point of LT can be applied safely with regards to steroid resistant acute rejections within 30 days after LT. **(II) **The secondary aim is to provide a therapeutic strategy that can improve or at least preserve an impaired renal function. **(III) **In a next consecutive sequential step we plan to perform a prospectively randomized 3-armed pilot-study that compares "bottom-up" CNI-free and CNI-containing IS regimens after LT in patients with impaired renal function and high-MELD-scores at the time-point of LT which would mean a change in paradigm from "top-down" to "bottom-up" IS strategies in at least a high risk population undergoing LT.

Reducing the risk for severe perioperative renal dysfunction (requiring dialysis) can be beneficial for patients with impaired renal function prior LT. It is likely that the early avoidance and latter "bottom-up" introduction of CNI and mTOR-inhibitors (everolimus or sirolimus) also reduces the incidence of early infectious complications, occurrence of hypertension, post-transplant diabetes mellitus and maybe decreases the risk for post transplant malignancies, the leading cause of death in patients undergoing solid organ transplantation.

## Methods and Design

### General Considerations and Study Population

This is a single-center study concept consisting of a prospective single-armed two-step pilot-trial (**PATRON07**) investigating safety and feasibility of a CNI-free, "bottom-up" IS strategy in patients undergoing LT with renal impairment prior to LT. Patients will be followed-up for one year after transplantation each. Since there is no clinical evidence for this IS approach, we decided to first perform an uncontrolled pilot-study investigating the safety and feasibility of a completely CNI-free approach

### Objectives of the study concept

The objective of **PATRON07 **is to evaluate a de novo CNI-free immunosuppressive regimen based on induction therapy with anti-CD25 monoclonal anti- body, mycophenolate mofetil (MMF/MPA), and delayed mTOR-inhibition. The primary endpoint is defined as the incidence of steroid-resistant acute rejection within the first 30 days after liver transplantation. It reflects the early potential and feasibility of the proposed immunosuppressive regimen with regards to safety and efficacy. In a liver transplant setting an acute rejection can be controlled with steroid treatment and does not necessarily mean an irreversible damage to the liver. Secondary objectives include the incidence of acute rejection(s), the number and the timing of acute rejections per patient within the first year after transplantation. A critical secondary endpoint will be the development of renal function at 1 week, 1, 3, 6 and 12 months after liver transplantation. This includes information on the number of patients requiring renal replacement therapy and its duration. During follow-up of 1 year liver allograft function, infectious complications, treatment failures defined as introduction of CNIs as well as side-effects affecting the hematopoetic system, tolerability, impaired wound-healing, the incidence of hepatic artery thrombosis and mortality will be explicitly documented and investigated.

### Trial Population

The collective we are aiming at are patients older than 18 years with a preexisting renal impairment at the time of LT. Patients will be eligible if the eGFR < 50 ml/min (Cockroft-Gault) and/or their serum creatinine levels > 1.5 mg/dL.

### Eligibility

Inclusion and exclusion criteria for **PATRON07 **are shown in table 1. Patients will be screened consecutively on the liver waiting list at Regensburg University and asked for their willingness to participate in this trial.

**Table 1 T1:** Key In- and Exclusion Criteria for PATRON07 and BUILT_01

Inclusion Criteria	Exclusion Criteria
Patients undergoing primary liver transplantation.	Patients with pre-transplant renal replacement therapy > 14 days.

Patients older than 18 years.	Patients with platelets < 50.000/nl.

eGFR < 50 ml/min at the time point of transplantation	Patients with triglycerides > 350 mg/dl and cholesterol > 300 mg/dl refractory to optimal medical treatment prior to initiation of therapy with mTOR inhibition.

Serum creatinine levels > 1.5 mg/dL at the time-point of transplantation	Multiple organ graft recipients.

Patients with eGFR < 50 ml/min at the time point of transplantation or Serum creatinine levels > 1.5 mg/dL at the time-point of transplantation	Patients with signs of a hepatic artery stenosis directly prior to initiation of therapy with Sirolimus.

	Patients with a psychological, familial, sociologic or geographic condition potentially hampering compliance with the study protocol and follow-up schedule.
	
	Patients under guardianship (e.g. individuals who are not able to freely give their informed consent).

### Consent

Patients on the waiting list meeting the inclusion and none of the exclusion criteria will be informed about the possibility of participating in either **PATRON07**. They will be fully informed about the trial, the procedures, risks, potential benefits and treatment alternatives as well as the study management, insurance and documentation of personal data with regard to meeting data protection legislation.

### Procedures of minimizing bias

**PATRON07 **is a non-controlled prospective trial at a single high volume liver transplant -center, which will reduce bias due to surgical learning effects.

### Interventions

#### Pre- and Intraoperative Data

Baseline data will be documented including demographics, medical history, current medication, metabolic, liver and renal function as well as history of renal treatment. Intraoperative data (warm and cold ischemic times, blood-loss, requirement for blood products, incision suture times) and donor data (age, sodium, gamma-GT, body-mass index, infectious status) will be also documented.

#### Treatment Regimen

Prior to reperfusion 500 mg Prednisolone will be administered i.v. After the transplantation, a combination of anti-CD25-mAB (*basiliximab 20 mg on day 0 and day 4 after the procedure*), and MMF *2 g/d*, *2 applications per day i.v., later conversion to oral intake*) will be applied. On day 10 after LT *Sirolimus *will be introduced with a loading dose of 5 mg/d. Thereafter a dosage of 2 mg/d will be administered, aiming at 24 hours trough-levels for *Sirolimus *between 4 and 8 ng/mL. Steroids will be started on day 1 after transplantation with 1 mg/kg BW and will be tapered every 2 days for 5 mg to a dosage of 20 mg and for 2.5 mg every two days to 7.5 mg. Thereafter the dosage will be reduced to 5 mg and 2.5 mg for 1 week each and eliminated thereafter. Additionally, every patient with risk constellation will receive cytomegalovirus (CMV) prophylaxis and prophylaxis against Pneumocystis carinii infection during the first 3 months after liver transplantation (Figure 1).

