**Figure 1 F1:**
[figure not shown]
**IS treatment regimen for PATRON07**. Basiliximab will be applied on day 0 and 4 after transplantation as 20 mg i.v. application, MMF will be applied as 2 g/d bid, center-specific steroids will be applied and tapered by month 6 after LT, Sirolimus will no be started prior to day 10 after LT aiming at trough-levels of 4 to 10 ng/ml.

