#### Follow-Up

Every patient will be followed up for 1 year after transplantation. The primary end-point will be at 30 days after transplantation (Steroid resistant acute rejection). During the first 30 days after transplantation there will be 9 visits where laboratory values (liver, renal and metabolic function, sirolimus trough levels), adverse events and rejection episodes will be recorded. Additionally there will be an ultrasound on day 1 after liver transplantation and on day 10 prior to the initiation of sirolimus to exclude hepatic artery thrombosis. Between day 30 and 1 year after liver transplantation the patient will be followed up to evaluate the long time outcome and secondary objectives of the trial. Table 2 gives an overview of planned examinations during follow-up.

**Table 2 T2:** Follow-up and planned interventions for PATRON 07

	Day 0	Day 1	Day 2	Day 3	Day 4	Day 10	Day 14/15	Day 20/21	Day 25/26	Day 30	Month 3	Month 6	Month 12
**Medical History^1^**	X												

**Transplant Data**	X												

**eGFR**	X	X	X	X	X	X	X	X	X	X	X	X	X

**Laboratory^2^**	X	X	X	X	X	X	X	X	X	X	X	X	X

**Ultrasound^3^**	X	X				X					X	X	X

**Rejection^4^**		X	X	X	X	X	X	X	X	X	X	X	X

**AE**	X	X	X	X	X	X	X	X	X	X	X	X	X

**Sirolimus trough levels (4-10 ng/mL)**							X	X	X	X	X	X	X

1: focusing on liver disease, infectious history, concomitant renal disease

2: Na, K, creatinine, urea, GOT, GPT, AP, yGT, bilirubin, CHE, LDH, Quick, pTT, Hb, leucocytes, platelets, cholesterole and triglycerides (day 0 and 30)

3: Additional examinations in case of pathologic findings or indication.

4. laboratory signs of rejection (if suspected confirmed by biopsy)

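### The sirolimus trough target is 4–8 ng/mL in the treatment text but 4–10 ng/mL in the Figure 1 legend and Table 2; the two steroid descriptions also need aligning

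*Protocol article*

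**What the plan says.** **Sirolimus.** The protocol article states a trough range in three places:

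- Treatment Regimen: troughs "between 4 and 8 ng/mL".
- Figure 1 legend: "aiming at trough-levels of 4 to 10 ng/ml".
- Follow-Up, Table 2: the monitoring row label begins "Sirolimus trough levels (4-10 ng/mL".

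**Steroids.** Treatment Regimen gives a fixed schedule. The start is "Steroids will be started on day 1 after transplantation with 1 mg/kg BW". The dose then "will be tapered every 2 days for 5 mg to a dosage of 20 mg and for 2.5 mg every two days to 7.5 mg" and is finally "reduced to 5 mg and 2.5 mg for 1 week each and eliminated thereafter". The Figure 1 legend says instead: "center-specific steroids will be applied and tapered by month 6 after LT".

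The article does not say which statement takes precedence in either case.

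**The concern.** In an uncontrolled trial, the result is the event rate under one defined regimen. Sirolimus exposure is part of that definition. The trial's rationale is to keep early immunosuppression low, so the upper end of the target range matters. If the text and the visit schedule give different upper limits, a reader cannot say which exposure the 30-day rejection rate and the one-year renal, infectious, hematologic and wound-healing outcomes belong to. The article presents the results as a possible basis for a later randomized trial, which would need one reproducible regimen.

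The steroid wording raises the same question in weaker form: is the regimen the fixed short taper, or a center-specific course that may run to month 6?

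**Working it through.** **1. The plan's own figures.** Statistical Analysis gives 9 patients in stage 1 (continue with 8 or more responders) and 29 in total (reject H0 with 27 or more). It states a type I error of 0.049 at p0 = 0.80 and a type II error of 0.198 at p1 = 0.95. With X1 the stage 1 responders out of 9 and X2 the stage 2 responders out of 20:

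P(reject H0) = P(X1 = 8)·P(X2 ≥ 19) + P(X1 = 9)·P(X2 ≥ 18)

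- p = 0.80: 0.3020 × 0.0692 + 0.1342 × 0.2061 = 0.0486 (stated 0.049).
- p = 0.95: 0.2985 × 0.7358 + 0.6302 × 0.9245 = 0.8024, so the type II error is 0.1976 (stated 0.198).

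Both figures reproduce. Neither uses the trough range or the steroid schedule.

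**2. Trough ranges side by side.**

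| Place | Range (ng/mL) | Width |
|---|---|---|
| Treatment Regimen | 4–8 | 4 |
| Figure 1 legend | 4–10 | 6 |
| Table 2 row | 4–10 | 6 |

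The lower limit is common to all three. The upper limit differs by 2 ng/mL (2/8 = 25%), and the wider window is 6/4 = 1.5 times the narrower. Only values above 8 and up to 10 ng/mL are classified differently.

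Table 2 schedules troughs on days 14/15, 20/21, 25/26 and 30 and at months 3, 6 and 12. That is seven visits, four of them within the first 30 days.

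**3. Length of the fixed taper.** The start dose is per kilogram and the article gives no body weights, so weight W (kg) is an assumption. Each dose is held for 2 days until the last two weekly steps.

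- From W mg down to just above 20 mg: 2 × (W − 20)/5 days.
- 20, 17.5, 15, 12.5, 10 and 7.5 mg: 6 × 2 = 12 days.
- 5 mg and 2.5 mg: 7 + 7 = 14 days.

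Last steroid day = 0.4 × (W − 20) + 26 = 0.4W + 18.

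| Assumed weight (kg) | Last steroid day |
|---|---|
| 50 | 38 |
| 75 | 48 |
| 100 | 58 |
| 130 | 70 |

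To run to about day 180, the taper would need 0.4W + 18 = 180, so W = 405 kg. The fixed taper therefore does not itself describe a six-month course.

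**4. Conditional steroid gap.** If month 6 were the actual end of steroids (about day 180), the difference would be 180 − 58 = 122 days at 100 kg and 180 − 38 = 142 days at 50 kg. If month 6 is only an outer limit, the taper meets it and the difference is zero.

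**The case against.** **The steroid statements can be reconciled.** Tapered by month 6 can mean no later than month 6. In a single-center trial, center-specific can simply mean the schedule printed in the text. This stands. A reader might infer a contradiction of about four months in steroid exposure, but the legend does not say that steroids continue until month 6. What remains is loose wording that supports two readings. Moreover, for the weights of 50 to 130 kg tabulated above, the fixed taper is still running at day 30, so any difference in its end date falls after the primary window.

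**The sirolimus start is not in conflict.** A reader might also set the text's start on day 10 against the legend's statement that sirolimus is not started before day 10. A start on day 10 satisfies both, so no contradiction can be claimed.

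**Nothing in the primary test changes.** The confirmatory analysis is by intention to treat on steroid-resistant rejection. Whether 9 ng/mL counts as on or off target alters no patient's responder status. The article also describes no adherence analysis or safety rule based on troughs. All this stands, and it limits the severity. A reader might infer that the safety or adherence results would be unreadable, but that would need an analysis the article does not describe.

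**The article condenses a full protocol that is not shown.** It therefore cannot be established that clinicians worked to two targets. That is fair, but the printed article still states two ranges, one of them in two separate places including the visit schedule. This is a contradiction in stated text, not a detail left to another document.

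**Conclusion.** The sirolimus trough target is contradictory: 4–8 ng/mL in one place and 4–10 ng/mL in two. The disputed band is above 8 and up to 10 ng/mL, and it applies at seven scheduled visits, four of them within the primary endpoint window. This rests on the printed text alone and needs no assumption.

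The steroid point is secondary. The fixed taper ends at about day 38 to 58 for assumed weights of 50 to 100 kg, and it agrees with the legend only if month 6 is an outer limit. The gap of about four months exists only if month 6 is the actual end of treatment.

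The harm is an inconsistently defined regimen in a single-arm trial. Decision rules, type I error and power are untouched, so this is a point that should be fixed rather than one that invalidates the design. The documents do not show which range or schedule was intended, and this review takes no position on that.

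**What to change.** - Reconcile Treatment Regimen, the Figure 1 legend and Table 2 so that one sirolimus trough range appears in all three. The value is for the clinical team to decide.
- Give one steroid description. If month 6 is an outer limit on the fixed taper, say so. If it is the planned end of steroids, the text and the legend must be brought together.
- Do this before stage 2 opens. The Current status section reports 9 patients included and the data being cleaned, so the timing is right.
- Record which trough target and steroid schedule the first 9 patients followed, so that a reader can judge whether both stages of the 29-patient decision describe one regimen. If they differ, report it with the results.

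The cost is a wording correction or minor amendment and a note to file for the stage 1 patients. Sample size, endpoint and decision rules do not change.

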**Figure 1 F1:**
[figure not shown]
**IS treatment regimen for PATRON07**. Basiliximab will be applied on day 0 and 4 after transplantation as 20 mg i.v. application, MMF will be applied as 2 g/d bid, center-specific steroids will be applied and tapered by month 6 after LT, Sirolimus will no be started prior to day 10 after LT aiming at trough-levels of 4 to 10 ng/ml.

#### Follow-Up

Every patient will be followed up for 1 year after transplantation. The primary end-point will be at 30 days after transplantation (Steroid resistant acute rejection). During the first 30 days after transplantation there will be 9 visits where laboratory values (liver, renal and metabolic function, sirolimus trough levels), adverse events and rejection episodes will be recorded. Additionally there will be an ultrasound on day 1 after liver transplantation and on day 10 prior to the initiation of sirolimus to exclude hepatic artery thrombosis. Between day 30 and 1 year after liver transplantation the patient will be followed up to evaluate the long time outcome and secondary objectives of the trial. Table 2 gives an overview of planned examinations during follow-up.

**Table 2 T2:** Follow-up and planned interventions for PATRON 07

	Day 0	Day 1	Day 2	Day 3	Day 4	Day 10	Day 14/15	Day 20/21	Day 25/26	Day 30	Month 3	Month 6	Month 12
**Medical History^1^**	X												

**Transplant Data**	X												

**eGFR**	X	X	X	X	X	X	X	X	X	X	X	X	X

**Laboratory^2^**	X	X	X	X	X	X	X	X	X	X	X	X	X

**Ultrasound^3^**	X	X				X					X	X	X

**Rejection^4^**		X	X	X	X	X	X	X	X	X	X	X	X

**AE**	X	X	X	X	X	X	X	X	X	X	X	X	X

**Sirolimus trough levels (4-10 ng/mL)**							X	X	X	X	X	X	X

1: focusing on liver disease, infectious history, concomitant renal disease

2: Na, K, creatinine, urea, GOT, GPT, AP, yGT, bilirubin, CHE, LDH, Quick, pTT, Hb, leucocytes, platelets, cholesterole and triglycerides (day 0 and 30)

3: Additional examinations in case of pathologic findings or indication.

4. laboratory signs of rejection (if suspected confirmed by biopsy)

### Clinical Sites

The study will be carried out at Regensburg University Medical Center.

### Safety aspects

All information and observations collected during the follow-up visits, as well as spontaneous reports from the patient, relatives or any other medical staff will be documented. Is an event serious (SAE) or suspected and unexpected (SUSAR) the particular authorities (BfArM [Bundesbehörde für Arzneimittel] and the Regensburg University Ethics Committee) will be informed. In case the safety and/or efficacy of the proposed treatment regimen will fail, the patient has to be switched to the center specific treatment regimen that potentially provides highest security with regard to safety and efficacy. Usually, this regimen will be based on a CNI. To evaluate the safety and efficacy of the proposed immunosuppressive regimen, a data safety monitoring board will be set up. After every third patient that finished the first 30 days period of the study, the monitoring board will receive data on efficacy and safety obtained from the patients. The board will consist of two physicians (one nephrologist and one hepatologist), who are both not involved in the study and independent from the conduct of the trial.

